## Reporting Procedures for Serious Adverse Events

SAE reporting will cover the period from randomisation and throughout tapering phase until the study nicardipine/placebo has been stopped.

All SAEs must be reported to the Research Team within 24 hours of the researcher becoming aware of the event. The psychiatrist will be asked to complete an SAE Form with the information available at the time of initial reporting and his/her opinion of relatedness and expectedness. S(he) will be asked to supplement this with additional information as it becomes available.

Receipt of an initial SAE report by the OxCaMS RA or NIHR-CRF Lead Nurse for OxCaMS will be acknowledged within 1 working day of receipt and the CI (or delegate) will make an immediate assessment of relatedness and expectedness. The CI will continue to review supplementary information as it is received.

The Chair of the Trial Steering Committee (see 10.6) will be sent details of all SAEs for review by the Committee weekly.

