Participant will also be asked to complete daily and weekly measures of mood in order to allow us to control for any changes is mood as we are wanting to explore the direct effect of calcium channel antagonism unconfounded by mood. Daily mood will be recorded using the short form of the positive and negative symptom scale (PANAS [37]) delivered on an iPad. The PANAS 10 item is a self-report scale which is widely used in psychiatric research. Weekly mood measures will be completed using the True Colours system ([www.truecolours.nhs.uk](http://www.truecolours.nhs.uk)). True colours is a mood monitoring platform developed in Oxford which is uses validated clinical scales to assess depression (quick inventory of depressive symptoms) and mania (Altman mania rating scale [39]).

All participants will have a two-week period of participation prior to randomisation. This will allow us to assess the stability of their cognitive function and collect baseline mood, sleep and activity data.

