# SAFETY REPORTING

## Definitions

| **Adverse Event (AE)** | Any untoward medical occurrence in a participant to whom a medicinal product has been administered, including occurrences which are not necessarily caused by or related to that product. |
| --- | --- |
| **Adverse Reaction (AR)** | All adverse events judged by either the Investigator or the Sponsor as having a reasonable suspected causal relationship to an investigational medicinal product qualify as Adverse Reactions. The expression reasonable causal relationship means to convey in general that there is evidence or argument to suggest a causal relationship. |
| **Serious Adverse Event (SAE)** | A serious adverse event is any untoward medical occurrence that:   - results in death - is life-threatening - requires inpatient hospitalisation or prolongation of existing hospitalisation - results in persistent or significant disability/incapacity - consists of a congenital anomaly or birth defect.   Other ‘important medical events’ may also be considered serious if they jeopardise the participant or require an intervention to prevent one of the above consequences.  NOTE: The term "life-threatening" in the definition of "serious" refers to an event in which the participant was at risk of death at the time of the event; it does not refer to an event which hypothetically might have caused death if it were more severe. |
| **Serious Adverse Reaction (SAR)** | An adverse event that is both serious and, in the opinion of the reporting Investigator, believed with reasonable probability to be due to one of the study treatments, based on the information provided. |
| **Suspected Unexpected Serious Adverse Reaction (SUSAR)** | A serious adverse reaction the nature and severity of which is not consistent with the information about the medicinal product in question i.e.:   - in the case of a product with a marketing authorisation, in the summary of product characteristics (SmPC) for that product - in the case of any other investigational medicinal product, in the Investigator’s Brochure (IB) relating to the study in question. |

NB: to avoid confusion or misunderstanding of the difference between the terms “serious” and “severe”, the following note of clarification is provided: “Severe” is often used to describe intensity of a specific event, which may be of relatively minor medical significance. “Seriousness” is the regulatory definition supplied above.

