Any pregnancy occurring during the clinical study and the outcome of the pregnancy should be recorded and followed up for congenital abnormality or birth defect, at which point it would fall within the definition of “serious”.

Causality

The relationship of each adverse event to the study medication must be determined by a medically qualified individual according to the following definitions:

*Related:* The adverse event follows a reasonable temporal sequence from study medication administration, cannot reasonably be attributed to any other cause.

*Not Related*: The adverse event is probably produced by the participant’s clinical state or by other modes of therapy administered to the participant.

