## SUSAR Reporting

A serious adverse event (SAE) occurring to a participant should be reported to the REC that gave a favourable opinion of the study where in the opinion of the Chief Investigator the event was ‘related’ (resulted from administration of any of the research procedures) and ‘unexpected’ in relation to those procedures. Reports of related and unexpected SAEs should be submitted within 15 working days of the Chief Investigator becoming aware of the event, using the HRA [report of serious adverse event](http://www.nres.npsa.nhs.uk/docs/forms/Safety_Report_Form_(non-CTIMPs).doc) form (see HRA website).

See Appendix C for a SAE reporting flow-chart.

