# Appendix B: Schedule of Procedures

| Attendance number | **1** | **2** | **3** | **4** |
| --- | --- | --- | --- | --- |
| Timeline (days) | **0** | **14** | **28** |  |
| Window (days) |  | **±2** | **±2** |  |
| Informed consent | ✓ |  |  |  |
| Demographics | ✓ |  |  |  |
| Diagnosis (MINI) | ✓ |  |  |  |
| Medical history | ✓ |  |  |  |
| Physical examination | ✓ | ✓ |  |  |
| ECG | ✓ |  | ✓ |  |
| Vital signs and BMI | ✓ | ✓ |  |  |
| Eligibility assessment | ✓ | ✓ |  |  |
| Follow-up call |  |  |  | ✓ |
| Personality disorder screen | ✓ |  |  |  |
| ADHD screen | ✓ |  |  |  |
|  |  |  |  |  |
| Neuropsychological tests | ✓ |  | ✓ |  |
| Randomisation |  | ✓ |  |  |
| True Colours | **✓** Weekly | | |  |
| PANAS | **✓** Daily | | |  |
| Cognitive tests | **✓** Daily | | |  |
| Carry activity monitor | **✓** Daily (with regular data downloads) | | |  |
| Concomitant medications | ✓ | ✓ | ✓ |  |
| Dispensing study drugs and pill count |  | ✓ | ✓ |  |
| Adverse Event check |  | ✓ | ✓ | ✓ |
| MEG |  | ✓* | ✓ |  |
| MRI |  | ✓* | ✓ |  |
| Sleep questionnaire | ✓ | ✓ | ✓ |  |
| Sleep Diary card commenced | ✓ | ✓ |  |  |
| Sleep Diary card completed & returned |  |  | ✓ |  |
| ePatch** | ✓ | ✓ |  |  |
| Portable blood pressure monitor*** |  | ✓ |  |  |
| Blood tests | ✓ |  | ✓ |  |
| Devices returned |  |  | ✓ |  |

- *MEG and MRI scan prior to taking any study medication.
- ** Wear for 72 hours
- *** Participants to record blood pressure once daily throughout two-week randomisation phase

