# Appendix C: SAE Reporting Flow Chart

**Adverse event**

**Adverse Event**

**No further action**

**Related to IMP?**

**Serious? (See box)**

**Expedited report to REC and Sponsor within:
 - 7 days if fatal/life-threatening, - 15 days if not**

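### SAE reporting opens only at randomisation and judges only the drug, although section 10.5 requires REC reports of unexpected SAEs from any research procedure

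*Protocol*

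**What the plan says.** **Window.** Section 10.3 of the protocol: "SAE reporting will cover the period from randomisation"; the window closes when study drug or placebo has been stopped. The 24-hour notice to the research team, the SAE form and the weekly steering-committee review are set out under that sentence. Only the start of the window is at issue here.

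**Participation before the window.** Section 4.2: "All participants will have a two-week period of participation prior to randomisation". Consent is taken at Visit 1, and the same visit brings blood sampling, an ECG, cognitive testing and the first 72-hour ePatch (sections 6.1 and 8.3, Appendix A). Appendix B puts Visit 1 at day 0, randomisation at day 14 and the final visit at day 28, the last two with a window of 2 days either way.

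**Definitions and causality.** In section 10.1 an adverse event is "Any untoward medical occurrence in a participant to whom a medicinal product has been administered". On causality: "The relationship of each adverse event to the study medication must be determined". Section 10.4 takes the Cardene SR product summary as the only reference for expectedness.

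**REC duty.** Section 10.5 requires a report when, in the Chief Investigator's opinion, an SAE was unexpected for the research procedures and "resulted from administration of any of the research procedures". It gives no start date and refers the reader to Appendix C.

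**Flow chart.** Both relatedness boxes legible in Appendix C read "Related to IMP", and the expectedness box points to the product summary.

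**Check at Visit 2.** Appendix B ticks "Adverse Event check" at attendances 2, 3 and 4. Appendix A also lists a check at the randomisation visit.

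**The concern.** Section 10.5 is written for a study in which any procedure can cause a reportable event. The steps that should feed it are written for a drug alone, and the collection window opens halfway through scheduled participation.

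Two kinds of event are affected. The first is any serious event between consent and randomisation, such as a hospital admission. Participants are selected for mood instability, and section 8.3 expects some to meet axis I/II criteria, so such an event is foreseeable even though those at significant immediate risk of self-harm are excluded. The second is a serious event caused by a procedure (venepuncture, ePatch, scan) at any time in the study.

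At stake is whether oversight of such events follows from the protocol or depends on an investigator going beyond section 10.3. The arm comparison is not affected.

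**Working it through.** The protocol states no figure that needs reproducing. The check compares the provisions, with one small calculation of time.

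**1. A serious event on day 7, in the run-in.**
- Section 10.3: outside the window, so the 24-hour report, the SAE form and committee review are not triggered as written.
- Section 10.1, AE row: not met, because no product has been given. The SAE row does not repeat that condition, so the two rows differ.
- Section 10.5: applies if the event was procedure-related and unexpected, because it has no start date.
- Appendices A and B: staff ask about adverse events at Visit 2, about a week later. Neither appendix says what to do with a serious event found then. Someone who consents and never attends Visit 2 is not asked at this check.

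**2. A serious event caused by a procedure after randomisation.**
- Section 10.3: inside the window, so it goes to the research team within 24 hours and to the committee chair whatever its cause. Section 10.6 says the same of the chair.
- Section 10.1, causality: the related category is tied to study medication. The not-related category names only clinical state or other therapy. An event caused by a procedure fits neither.
- Section 10.4: a drug's product summary cannot say what is expected of an ePatch, a blood draw or a scan, yet 10.5 judges expectedness against the procedures.
- Appendix C: no legible box asks about procedures, so nothing legible in the chart leads to the 10.5 report.

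The mention in section 10.2 of another suspect drug or device does not close this gap, because it covers only certain non-serious reactions.

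**3. Time before the window opens (inputs: Appendix B).**
Share = day of Visit 2 / day of Visit 3.
- As scheduled: 14/28 = 50%.
- Visit 2 early, Visit 3 late: (14 − 2)/(28 + 2) = 12/30 = 40%.
- Visit 2 late, Visit 3 early: (14 + 2)/(28 − 2) = 16/26 = 62%.
- Adding the one-week follow-up in the synopsis to the denominator: 14/(28 + 7) = 14/35 = 40%.

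The uncovered period is 12 to 16 days per randomised participant. The documents give no event rate, so this cannot be turned into a number of events.

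**The case against.** The strongest case on the other side is that little is really lost. No study drug is given in the run-in and its procedures are minor. Those at significant immediate risk of self-harm are excluded, and section 15.7 covers participants who become unwell. The Visit 2 check exists, 10.5 runs from the Chief Investigator's awareness, and nothing in 10.3 forbids reporting an earlier event. Opening SAE reporting at randomisation is then partly a design preference.

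Much of this stands, and it rules out several stronger readings that a reader might infer:
- That run-in serious events go uncaptured. The Visit 2 check can find them. What is missing is a defined route onward.
- That the provisions cannot all be followed. They are misaligned rather than mutually exclusive, since an investigator could report earlier than 10.3 asks.
- That procedure-related SAEs after randomisation never reach oversight. Sections 10.3 and 10.6 send all SAEs in the window to the team and the chair. The gap is in classification and in the step to the REC.
- That the trial loses a needed drug-free safety record. The concurrent placebo arm of 20 already serves as the comparator.

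Two limits also apply. Appendix C is legible only as separate boxes without arrows, so where a negative answer leads cannot be seen. Appendix A appears to list the pre-treatment scans under allocation, which may place them inside the window, so the run-in argument does not rely on them.

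What the objection does not answer is that 10.5 needs a judgement of procedure-relatedness that no other section provides, and that a check at about day 14 is no substitute for a 24-hour report.

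**Conclusion.** The point holds as a conflict within the stated safety rules. Followed as written, section 10.3 leaves serious events in the run-in without the 24-hour and steering-committee route. The causality scale, the expectedness reference and the legible part of Appendix C supply no judgement that would trigger the 10.5 report for a procedure-related SAE. The uncovered time is about half of the scheduled days to Visit 3, with a range of 40% to 62% under the visit windows. It should be corrected by amendment. The conclusion assumes that the missing arrows of Appendix C hide no procedure branch and that the window sentence in 10.3 governs the duties listed beneath it.

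**What to change.** Reconcile sections 10.1, 10.3, 10.4, 10.5 and Appendix C:
- **10.3:** start SAE reporting at signed consent.
- **10.1:** word the AE definition for a consented participant, and have relatedness judged separately for the study drug and for study procedures.
- **10.4:** keep the product summary as the reference for the drug, and judge procedure-related events against what is expected of the procedure, as 10.5 already does.
- **Appendix C:** make the relatedness box ask about the IMP or a study procedure, with a branch to the 10.5 report.
- **Appendices A and B:** state that a serious event found at the Visit 2 check goes to the SAE process.
- **Reporting of results:** tabulate events before the first dose separately, outside the arm comparison.

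The cost is a few sentences in an amendment, one extra field on the SAE form and probably a few extra reports. No visit, procedure or staff need be added.

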| **Treatment duration** | 2-week randomised phase |
| **Follow up duration** | 1 week |
| **Planned Accrual Period** | 2 years |
| **Intervention** | Nicardipine SR |
| **Formulation, Dose, Route of Administration** | Nicardipine sustained release 30mg taken twice daily.  Matched placebo. |

| **Objectives** | **Outcome Measures/Endpoints** |
| --- | --- |
| Primary objective:  To compare the effects of nicardipine and placebo on measures of cognitive instability.  . | Primary outcome measure: Cross sectional and longitudinal assessments of cognition |
| Secondary objectives  1. To compare the effects of nicardipine and placebo on variability in neural dynamics during MRI and MEG scans. This will include scans during resting state and whilst performing neuropsychological tasks.  2. To explore the effects of nicardipine on physical activity and sleep.  3. To develop a profile of calcium channel expression and calcium signalling with and without nicardipine treatment.  4.Heart rate variability  5. Mood instability | Secondary outcome measure   1. Blood oxygen level dependent signal during rest and during cognitive testing; induced and evoked field activity 2. Activity monitor measurements:   2a. Actigraphy data from a maximum of two wearable units, allowing analysis of indices of:   1. Frequency and amplitude of movements during daytime activity   ii. Categorisation of activity types.   1. Duration, timing, and quality of sleep.   2b. Sleep quality indicator questionnaire (SCI; self-report sleep measure (Espie, 2014)).  3. Measure effects of nicardipine on leucocyte calcium channel expression and calcium signalling  4. Change in R-R interval variability   1. Changes in mood instability as defined using root mean square of the successive differences (RMSSD) |

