## Post-study follow-up

Participants will be contacted following cessation of study treatment to review the status of any reported adverse events (AEs) and to check for any unreported AEs.

Please see Appendix A for a diagram of the participant pathway in the study and assessments at each visit.

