## 8.6. Post-study follow-up

Participants will be contacted within a fortnight of study completion, usually by phone, following cessation of study treatment to review the status of any reported Adverse Events and to check for any unreported AEs.

Please see Appendix B for a schedule of procedures during the study duration.

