## Definition of End of Study

The end of study is the date of the last post-study follow-up of the last participant.

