# NICARDIPINE

## Description

Nicardipine will be provided as Cardene SR 30mg capsules. Cardene SR 30mg capsules will be purchased from Oxford Pharmacy Stores. The Department of Psychiatry will (over-)encapsulate Cardene (to mask print on the capsule) and encapsulate matched placebo tablets. Each bottle will be assigned a unique randomisation number to ensure concealment of allocation.

*Nicardipine dose:* Following random allocation (see 8.6), nicardipine/placebo will be given at a dose of 60mg. This will be a stable dose throughout the study period. Participants will be instructed to take the capsules as two separate doses – one 30mg dose after breakfast and one 30mg dose at bedtime*. Nicardipine takes at least 3 days to reach steady state plasma levels.

* Capsules should be taken as near to 12 hours as possible after the previous dose.

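### Section 10.3 closes the SAE reporting period when study drug stops and refers to a taper that does not exist, although the protocol plans a later contact to look for unreported adverse events

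*Protocol*

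**What the plan says.** Section 10.3 of the protocol sets the period: "SAE reporting will cover the period from randomisation and throughout tapering phase until the study nicardipine/placebo has been stopped". No other section gives a start or an end for SAE reporting.

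The Nicardipine section, under its description of the product, sets 60 mg a day as two 30 mg doses and adds: "This will be a stable dose throughout the study period".

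Follow-up after the drug is planned in several places:

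- Section 6.5: participants are contacted after treatment ceases "to review the status of any reported adverse events (AEs) and to check for any unreported AEs".
- Section 8.6: "Participants will be contacted within a fortnight of study completion, usually by phone".
- Synopsis: "Follow up duration | 1 week".
- Appendix B: the row "Adverse Event check" is ticked at the fourth attendance, which is the follow-up call.
- Section 8.12: "The end of study is the date of the last post-study follow-up of the last participant".

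**The concern.** The SAE period closes before the study does. The follow-up contact exists partly to find events nobody has yet reported, and some of those may have begun after the last capsule. If one is serious, section 10.3 read literally places it outside the period, so the person making the call has no clear instruction on what to do with it. The mention of a tapering phase adds to the doubt, because the period is described partly by a phase that no participant goes through.

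What is at stake is consistent handling of serious events in the follow-up interval. The point has no bearing on the cognitive or imaging outcomes.

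**Working it through.** The protocol gives no figure to reproduce here. The check is a comparison of sections and a short timeline.

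**Is there a taper?** The study design (section 6), the procedures (section 8), the participant pathway (Appendix A) and the schedule (Appendix B) contain none. The dose is described as stable. The only other hint of a dose change is the participant card described in Appendix G, which is to be replaced if the dose changes. That does not create a tapering phase. The reference in 10.3 has nothing to attach to.

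**Where does the period end relative to follow-up?** Inputs: 2 weeks of treatment (synopsis); follow-up of 1 week (synopsis); contact no later than a fortnight after study completion (section 8.6). Count days from randomisation and take the last capsule as day 14, close to study completion.

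- Period under 10.3: day 0 to day 14.
- Contact at 1 week: 14 + 7 = day 21. Uncovered interval: 21 − 14 = 7 days.
- Contact at the latest date under 8.6: 14 + 14 = day 28. Uncovered interval: 28 − 14 = 14 days.

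The second figure is an upper limit. Section 8.6 sets a deadline, so an earlier call also satisfies it and the interval could be shorter than 7 days. The fortnight runs from study completion and not from the last capsule, which is why the figures are approximate. The ±2-day visit windows in Appendix B change the length of dosing but not the length of the interval after it.

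**Do the other safety sections fill the gap?**

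- Section 10.5 sets the ethics committee deadline by awareness: "Reports of related and unexpected SAEs should be submitted within 15 working days of the Chief Investigator becoming aware of the event". It gives no closing date for onset.
- Section 10.6 sends all SAEs to the committee chair and uses the yellow card system for SAEs related to study drug. It gives no period.
- Appendix C repeats the 24-hour report to the research team and shows continuing steering committee review. It gives no period.
- Section 13 says that the steering committee reviews SAE reports. It gives no period.

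These sections say who is told and how fast. None says until when, so they neither extend the 10.3 period nor contradict it.

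**The case against.** The strongest reply is that section 10.3 itself goes on to require that all SAEs reach the research team within 24 hours and that details of all SAEs go to the committee chair. Read broadly, those sentences already reach a late event. Read as limited by the opening sentence, the whole protocol agrees on one period that simply ends with the drug. Either way, silence in 10.5, 10.6 and Appendix C is not a contradiction. This stands, and it is why the point is one of ambiguity. It does not rescue the opening sentence: on the broad reading that sentence has no function, and on the narrow reading it leaves out an interval that the protocol deliberately monitors.

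A reader might infer more than the text supports:

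- *That late SAEs will be lost.* The 24-hour report, the chair, the yellow card and the ethics committee route remain available in sections without an end date. Steering committee review is not confined to 10.3 either; only its weekly timing is.
- *That the two follow-up statements contradict each other.* A call at one week satisfies both.
- *That 7/21 = 33% to 14/28 = 50% of each participant's observation is uncovered.* Those ratios treat a deadline as a fixed duration, and they are shares of time and not of events.
- *That pregnancies and early stoppers are left without follow-up.* Section 10.1 separately requires pregnancy outcomes to be recorded and followed, and section 6.5 does not restrict the contact to completers.

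The protocol also describes nicardipine at this dose as widely used with a well-documented safety profile, and it gives no SAE rate. Nothing suggests that many events would fall in the interval.

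**Conclusion.** The point holds as a defect in the safety wording. The only stated SAE period ends at drug cessation and cites a phase that does not exist, while the protocol schedules a later check for unreported events and ends the study there. A serious event starting in between is outside the stated period and its handling is unclear.

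The interval is about 7 days with a contact at one week and at most about 14 days under section 8.6. This assumes 14 days of dosing and a last capsule close to study completion. The number of events affected cannot be estimated from the document. The correction should be made because it is cheap and concerns participant safety; no effect on the efficacy analyses is claimed.

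**What to change.** Replace the opening sentence of section 10.3, removing the reference to tapering, with:

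> *SAEs are reported from randomisation up to the post-study follow-up contact, for every randomised participant, including those who stop study drug early, unless consent is withdrawn. SAEs suspected to be related to study drug are reported whenever the team becomes aware of them.*

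This ties the period to a contact that is already planned. The exception for withdrawn consent avoids making continued collection the default for people who have left the study. For those who stop the drug without withdrawing consent, the new sentence is a specific rule for SAEs alongside the general stop in data collection in section 8.11; a cross-reference there is a drafting choice.

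The cost is a small wording amendment through the Sponsor and the ethics committee, and possibly a few extra calls to early stoppers.
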